**Figure 2. F2:**
[figure not shown]
Design of virtual reality vaping cue scenes. (A) No social pressure: participants navigate a convenience store with subtle vaping cues (eg, posters, products). (B) Social pressure: participants attend a barbecue where peers vape and offer an e-cigarette.

##### Cue Scene Without Social Pressure

Participants are placed in a virtual convenience store where they are tasked with picking up items from a shopping list (eg, chips, sauces, and drinks) distributed across areas of the store. This task is designed to enhance ecological validity and introduce a mild cognitive distraction, allowing vaping cues to attract participants’ visual attention more naturally. Cue elements include vaping-related posters, vapes behind the counter, and individuals vaping outside the store, visible through the glass window.

##### Cue Scene With Social Pressure

Participants are immersed in a barbecue party with animated virtual humans, who function both as interaction partners and as background social groups within the scene [33]. Participants are prompted to engage with different clusters of characters and overhear conversations about food, vaping, and school stress. Several characters visibly vape and directly offer an e-cigarette to the participant. This scenario incorporates both visual and verbal peer pressure, reflecting common real-world contexts in which adolescents and young adults may be exposed to vaping.

### Software Development and Apparatus

The VR experience was developed in Unity 2021.3.15 (Unity Technologies) and run on a Windows 11 workstation (Intel i9-14900KF CPU, NVIDIA GeForce RTX 5080 GPU, 64 GB DDR5 RAM). The Meta Quest Pro (Meta Platforms Inc) will be used to deliver the eye-tracking–enabled VR scenes. Eye-gaze behavior will be captured via the headset’s integrated tracker using Oculus Movement software development kit v1.3.2. A set of regions of interest is predefined to register fixations on key stimuli (eg, vaping products, posters, and virtual characters). The system is optimized to minimize false negatives in fixation detection, accounting for the Quest Pro’s accuracy (mean 1.652°, SD 0.699°) when designing the room-scale experience [23,34].

Other physiological data, including EDA and HR, will be recorded using the Shimmer3 galvanic skin response + sensor (Shimmer Sensing) [35], a noninvasive, wrist-worn device placed on the participant’s nondominant hand. The device, worn on the nondominant wrist, measures EDA via galvanic skin response and estimates HR via a photoplethysmography pulse probe. Both signals are processed through validated internal functions within the Shimmer application programming interface to extract features such as skin conductance response (SCR) amplitude and HR metrics. This device is widely used in physiological and participatory research due to its portability and signal accuracy [36-38].

Virtual characters are designed in Character Creator 4 and animated in iClone 8 (Reallusion Inc) using LiveFace for facial motion capture combined with keyframe adjustments, ensuring naturalistic social interactions and emotional expressiveness within the VR environments.

### Recruitment

Participants will be recruited through a combination of physical flyers and digital advertisements disseminated via social media, group chats, and email lists. Flyers will be posted around the New Haven community and college campuses where young adults commonly gather. This multipronged approach will support the recruitment of individuals aged 18 to 21 years living near the study site who can travel for an in-person laboratory visit [39].

To recruit vapers, we will additionally use a snowball recruitment strategy. Because vaping commonly occurs in social settings (eg, college parties) [27], we will contact relevant student organizations to request the distribution of study information to their members. We will also reach out to local vaping retailers and convenience stores to request that they display study materials. Finally, we will reach out to research teams that conducted previous substance use research in and around the New Haven area to request assistance with sharing our recruitment flyer through their mailing lists.

Interested individuals will be directed to a Qualtrics screening questionnaire to determine eligibility. To ensure adequate representation of both vapers and nonvapers, enrollment will be monitored on a weekly basis and adjusted as needed.

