## Methods

### Study Design

This study will examine individuals’ psychological, behavioral, and physiological responses to e-cigarette cues in VR among young adults aged 18 to 21 years. We focus on this age range because the transition into early adulthood often brings increased exposure to vaping-related social contexts (eg, college gatherings) [27], and this pilot allows us to first test the paradigm in adults before adapting it for adolescent populations. A between-subjects design is used to compare current e-cigarette users and nonusers, with a within-subject, counterbalanced component to assess 2 cue conditions (with and without social pressure). This mixed-design approach enables testing of cue effects and group differences while controlling for individual variability.

Prior VR nicotine cue reactivity studies have reported medium-to-large effects for the response difference between user and nonuser groups [17,28]. Based on the relevant research and using G*Power 3.1 (Heinrich Heine University Düsseldorf) for a 2 (group: vapers vs nonvapers)×2 (cue condition: social pressure vs no social pressure) mixed design, we powered the study for the group × cue condition interaction (group×cue condition) assuming a medium effect (*f*=0.25; partial η-squared ≈ 0.06; power=0.80). We assumed a within-participant correlation of *r*=0.50 between cue conditions and a nonsphericity correction of *ε*=1.0 (sphericity is not applicable with 2 within-subject levels). This yields a minimum required sample of 34 (n=17 per group). To ensure robustness and account for potential data loss (eg, eye-tracking dropout and physiological artifacts), we plan to recruit 40 participants in total (n=20 vapers and n=20 nonvapers).

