##### Primary Analyses

For the primary aim of examining differences in psychological and physiological responses between vapers and nonvapers during VR cue exposure with and without social pressure, a mixed-model ANOVA will be conducted. Group (vapers vs nonvapers) will serve as the between-subjects factor, and cue condition (social pressure vs no social pressure) as the within-subjects factor. If the assumptions of normality or homogeneity of variance are violated, nonparametric alternatives such as the aligned rank transform ANOVA [55] will be used to preserve the ability to test interaction effects within the mixed design. Follow-up pairwise comparisons will be conducted with Bonferroni-adjusted *P* values.

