##### Secondary Analyses

For the secondary objective, we will assess associations between multimodal physiological measures and subjective vaping-related outcomes. Correlation and regression analyses will first be conducted to examine pairwise relationships among eye-gaze metrics (eg, total fixations and mean fixation duration), HR, EDA, and subjective measures (eg, craving, dependence scores, and motivation to quit or susceptibility to initiate use). Depending on data distribution, the Pearson or Spearman correlations will be used. Partial correlations or multiple regression models will account for potential covariates such as age, gender, and other substance use.

To further explore multivariate relationships between physiological responses and vaping-related outcomes, exploratory regularized regression analyses will be conducted. Given the pilot sample size, we will use regularized logistic regression with the least absolute shrinkage and selection operator to examine whether aggregated physiological and subjective measures are associated with vaping status (vaper vs nonvaper). Candidate predictors will include summary features derived from eye-gaze behavior (eg, fixation count, proportion of fixation duration on vaping-related cues, and time to first fixation), HRV metrics derived from photoplethysmography signals (including time-domain indices such as root mean square of successive differences and frequency-domain measures such as low-frequency to high-frequency ratio), EDA (eg, mean number of SCRs, mean SCR amplitude, and mean skin conductance level), and relevant subjective responses (eg, craving, presence, and social presence).

Physiological signals will undergo standard preprocessing procedures, including signal quality checks, removal of segments affected by motion artifacts or signal instability, and aggregation into scene-level summary features. Participants will be excluded if more than 15% of their physiological data is missing, and EDA signals will be removed if more than 15% of values are zero or negative, indicating poor sensor contact [56,57]. The regularization parameter will be selected using cross-validation to reduce overfitting [58]. Given the exploratory nature of this analysis and the modest sample size, findings will be interpreted cautiously and used to identify candidate multimodal markers for future confirmatory studies rather than to develop generalizable prediction models.

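### Recruitment channels aimed at vapers, with no covariate in the primary ANOVA, may mix the between-group effect with recruitment-linked differences

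*Protocol article*

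**What the plan says.** The Recruitment section of the protocol article begins with channels for everyone: "Participants will be recruited through a combination of physical flyers and digital advertisements disseminated via social media, group chats, and email lists". It then turns to one group: "To recruit vapers, we will additionally use a snowball recruitment strategy". Three further routes follow under that purpose:

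- student organizations, chosen because vaping is common in social settings: "we will contact relevant student organizations to request the distribution of study information to their members"
- shops: "We will also reach out to local vaping retailers and convenience stores to request that they display study materials"
- lists held by other investigators: "we will reach out to research teams that conducted previous substance use research in and around the New Haven area"

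All candidates pass through one online screener. Enrolment is reviewed weekly so that both groups are adequately represented. No matching on any characteristic is described.

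Under Primary Analyses, "Group (vapers vs nonvapers) will serve as the between-subjects factor", cue condition is the within-subjects factor, and no covariate is named. Under Secondary Analyses, partial correlations or multiple regression will "account for potential covariates such as age, gender, and other substance use". Study Population and Study Flow adds that nicotine use in other forms is assessed at baseline so that it can be handled in the analysis, but the primary model contains no such term.

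The Primary Aim predicts stronger responses in vapers than in nonvapers across both scenes. Study Design says that the mixed design "enables testing of cue effects and group differences while controlling for individual variability". Limitations mentions a mostly student sample and the disclosure of gaze tracking, but not recruitment that differs by group.

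**The concern.** Vaping status is observed, not assigned, so the comparison of vapers with nonvapers is only as clean as the similarity of the two groups in other respects. Routes aimed at one group can make the groups differ in gender, age, other substance use, social habits or experience of research.

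Some of these routes also resemble the stimuli. The scenes are a convenience store and a barbecue party. The added routes include convenience stores, and student organizations approached because vaping occurs at gatherings such as college parties. Familiarity with such settings could plausibly affect presence, social presence and arousal, which are primary-aim outcomes with a predicted direction.

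At stake is the main question of the study, whether responses distinguish vapers from nonvapers. A group difference could be read as a marker of vaping when part of it marks how people were found. The Study Design sentence makes this easier to miss, because it can be read as saying that individual differences are controlled for the group comparison as well.

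**Working it through.** **1. Which effects are exposed.** Write a participant's response in a scene as a person-level part plus a scene part.

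- *Cue-condition effect.* Each person is compared with himself or herself, so the person-level part cancels. Recruitment-linked traits do not bias this contrast.
- *Group main effect.* This compares the two-scene means of different people. A trait that differs between groups and relates to the outcome passes straight into it. This is the effect that the Primary Aim predicts across both scenes.
- *Group by cue interaction.* This compares within-person differences between groups. A trait that shifts both scenes equally cancels. Bias arises only if the trait changes the response to social pressure.

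The Study Design statement about individual variability therefore holds for the cue-condition effect and not for the group effect.

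**2. The plan's own figure.** Inputs from Study Design: f = 0.25, r = 0.50, two groups, two conditions, power 0.80. Alpha is not stated in the article; 0.05 is assumed. The noncentrality of the interaction is f² × N × 2 / (1 − r).

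- N = 34: 0.0625 × 34 × 2 / 0.5 = 8.5, power 0.807
- N = 32: noncentrality 8.0, power 0.781

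The stated minimum of 34 is reproduced. The sample size is not in error.

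**3. False-positive rate of the group test under an assumed bias.** Suppose there is no true vaping effect, and recruitment-linked differences shift the group contrast by b, in SDs of a single-scene outcome.

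- SD of the two-scene mean: √((1 + r)/2) = √0.75 = 0.866
- Noncentrality of the two-sample t with 20 per group: (b / 0.866) × √(20/2)
- Two-sided critical value with 38 degrees of freedom: 2.024

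| Assumed bias b | Noncentrality | False-positive rate |
|---|---|---|
| 0 | 0 | 5% |
| 0.15 SD | 0.548 | 8.3% |
| 0.30 SD | 1.095 | 18.7% |

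One way to reach 0.15 SD is a 30-point gender imbalance combined with a 0.5 SD gender difference in the outcome: 0.30 × 0.5 = 0.15. Reaching 0.30 SD takes two such traits acting in the same direction. Neither the imbalance nor the gender difference comes from the documents.

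**4. A second scale.** Let D be the standardized group difference on a trait and c the trait's correlation with the two-scene mean, so that the bias is D × c in SDs of that mean. The false-positive rate is 5.4% for D = 0.3, c = 0.2; 7.5% for D = 0.5, c = 0.3; 12% for D = 0.5, c = 0.5; and 34% for D = 1.0, c = 0.5. It runs from negligible to serious, depending wholly on the assumptions.

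**5. What adjustment costs.** For a group main effect of f = 0.25 at N = 40, the unadjusted noncentrality is 0.0625 × 40 × 2 / 1.5 = 3.33 and power is 0.43. With one covariate (37 error degrees of freedom, variance inflation 1 + D²/4), power runs from about 0.36 to 0.53 over D = 0.3 to 1.0 and c = 0 to 0.5. The loss or gain depends on how far the groups differ on the covariate and how well it predicts the outcome.

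**The case against.** **The sources overlap.** The general channels serve both groups, the vaper routes come on top of them, nothing closes those routes to nonvapers, and everyone uses the same screener. This stands. A reader might infer two separate source populations. The text supports only extra effort towards the harder-to-reach group, which may still shift its composition.

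**Leakage in one group.** A reader might also infer that snowballing lets vapers alone arrive knowing the scenes and the gaze tracking. The documents do not support this. Limitations says that gaze measurement is disclosed to participants before the VR session, with no restriction by group, and talk about scene content could travel through campuses and group chats in either group. Foreknowledge is possible, but it is not stated.

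**The size is assumed.** This stands. Adding several traits to reach larger biases ignores traits that overlap or oppose each other. Nor should the bias be measured against the medium effect in Study Design, since that f = 0.25 refers to the interaction.

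**Partly handled already.** Other nicotine use, substance use, impulsivity and emotion regulation are measured, covariates are named for the secondary analyses, and the status-prediction model is labelled exploratory. Sensitivity analyses may sit in a plan not shown. This softens the point. However, the primary model is stated here without covariates that the same article names for other analyses, and a later analysis plan cannot undo unequal recruitment or recover a referral source that was never recorded.

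**Limits of matching.** Ages span only 18 to 21, so matching by year of age would gain little, and matching on gender cannot reach party familiarity. Both stand. Enrolment had reached 7 of 40 by March 2026, so a change of channels would be partial but would still cover most participants.

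**Conclusion.** The point holds in limited form. The added channels are aimed at vapers, balance is monitored only as group representation, and the primary ANOVA has no covariate. The between-group effect may therefore combine vaping status with recruitment-linked differences; the documents do not show that it does. The cue-condition effect is not exposed, and the powered interaction is exposed only through a trait that modifies the response to social pressure.

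The range of about 8% to 19% rests on an assumed bias of 0.15 to 0.30 SD, no true group effect, 20 per group, r = 0.50 and alpha 0.05. It illustrates sensitivity and does not estimate the bias in this study. The claim of control for individual variability needs correcting as far as it touches the group effect. The change is worth making because it is cheap and most participants were still to be enrolled in March 2026.

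**What to change.** 1. Report the primary group effect adjusted for age and gender, either in the primary model or as a prespecified sensitivity analysis beside it. Add a further sensitivity analysis for other substance use, which would also carry out the stated intention to account for other nicotine exposure.
2. For the remaining enrolment, send the student-organization and mailing-list invitations, and the referral requests, to never-vapers as well. Use the existing weekly monitoring to keep the gender mix similar in the two groups.
3. Record each participant's referral source, and ask participants at debriefing not to disclose scene content.
4. Amend Study Design to say that the design controls individual variability for the cue-condition effect and not for the group effect. List group-specific recruitment under Limitations.

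The cost is protocol wording, one or two degrees of freedom in the group comparison, and possibly slower nonvaper enrolment. With 40 participants only one or two covariates are affordable at a time, which is why other substance use goes into a separate analysis. Adjustment cannot remove unmeasured differences such as party familiarity.

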### Assessments

At the start of the laboratory visit, participants will complete the informed consent procedure and then part 1 of the assessment questionnaire. Part 1 contains self-report measures on vape perception, substance use intentions and behaviors, and psychosocial assessments (Table 1).

**Table 1. T1:** Baseline and trait-level measures assessing vaping-related behaviors, substance use, and psychosocial characteristics among participants.

Measures	Brief description of items	Response options
For vapers		
Intention to Quit E-cigarettes by *Motivation to Stop Scale (MTSS)* [40]	1 item: “Which of the following describes your intention regarding e-cigarette use?”	7 response options, ranging from (1) “I don’t want to stop using e-cigarettes” to (7) “I REALLY want to stop using e-cigarettes and intend to in the next month”
E-cigarette Dependence by *Penn State Electronic Cigarette Dependence Index measures* [41]	6 items (*α*=.51). An example is: “How many times per day do you usually use your electronic cigarette?”	7 response options, ranging from (1) “0‐4 times/day” to (7) “30+ times/day”
For nonvapers		
Future Addiction by adapted *Pierce Susceptibility Questionnaire* [42]	3 items. An example is: “If one of your best friends offered you an e-cigarette, would you smoke it?”	4-point Likert scale, ranging from (1) “Definitely yes” to (4) “Definitely not”
For all participants		
E-cigarette Perceived Harm and Addiction [43]	3 items. An example is: “How likely is someone to become addicted to e-cigarettes/vaping?”	4-point Likert scale, ranging from (1) “Unlikely” to (4) “Likely”
Other Substance Use (cigarettes, marijuana, alcohol) [44]	6 items. An example is: “How many days in the past 30 days have you smoked a cigarette?”	7 response options, ranging from (1) “0 day” to (7) “All 30 days”
Impulse behavior by *Short UPPS-P Impulsive Behavior Scale* [45]	20 items (*α*=0.74‐0.88), based on the following subscales: Negative urgency (4 items), Lack of perseverance (4 items), Lack of premeditation (4 items), Sensation seeking (4 items), Positive urgency (4 items)	4-point Likert scale, ranging from (1) “Strongly agree” to (4) “Strongly disagree.”
Emotional regulation by *Brief Difficulties in Emotion Regulation Scale (DERS-18)* [46]	18 items (*α*=0.77). An example is: “I pay attention to how I feel.”	5-point Likert scale, ranging from (1) “Almost Never” to (5) “Almost Always”

After each VR cue scene, participants will remove the headset and complete part 2 of the assessment questionnaire. Part 2 contains self-report measures on craving, presence, social presence, and system usability. An overview of the assessment used in the laboratory visit is listed in Table 2.

**Table 2. T2:** Post–VR cue exposure measures assessing craving, presence, social presence, and system usability.

Measures	Items	Response options
Measured twice, after each VR cue scene		
Craving for vaping or smoking e-cigarettes Visual Analog Scale (VAS) [47]	1 item: “I have a desire for vaping/having an e-cigarette right now.”	A visual scale, ranging from 0 (“Not at all”) to 100 (“Extremely”)
Adapted presence and social presence questionnaire from *Presence (IPQ)* and *Social Presence by Networked Minds Measure of Social Presence* [48,49]	1 item from IPQ measuring general presence: “In the computer-generated world I had a sense of ‘being there’” (general presence item from IPQ). 6 items from the co-presence subscale (*α*=0.84). An example is: “The virtual humans caught my attention.”	5-point Likert scale, ranging from (0) “Do not agree at all” to (4) “Very Likely”
Measured once, after all VR scenes		
System usability by V*irtual Reality System Usability Questionnaire (VRSUQ)* [50]	9 items (*α*=0.679‐0.896). An example is: “The system responded well to my manipulations as expected with no delays.”	5-point Likert scale, ranging from (1) “Strongly disagree” to (5) “Strongly agree”

Eye gaze and physiological data will be recorded continuously during both VR cue scenes as follows:

Eye-gaze behavior: raw eye-tracking data and gaze fixations on predefined regions of interest (eg, vaping-related cues) will be collected and processed into fixation-related metrics such as fixation count, duration, and dwell time.HR and heart rate variability (HRV) will be monitored as indicators of autonomic arousal. HRV will be further processed into standard time-domain metrics, including the root mean square of successive differences, which reflects short-term parasympathetic activity, as well as frequency-domain metrics such as the low-frequency–to–high-frequency ratio, commonly interpreted as an index of sympathovagal balance [51].EDA will also be recorded to measure autonomic arousal and decomposed into tonic skin conductance levels and phasic SCRs using continuous decomposition analysis [52].

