#### Primary Aim

The primary aim is to examine differences in psychological (craving, sense of presence, and social presence) and physiological (eye gaze, HR, and EDA) responses between young adults who currently vape and those who have never vaped during exposure to VR vaping cues presented with and without social pressure. We hypothesize that vapers will exhibit stronger craving, a greater sense of presence and social presence, increased visual attention to vaping cues, and heightened physiological arousal compared with nonvapers across both VR scenes. We further expect that both groups will show stronger psychological and physiological responses in the social pressure condition than in the no pressure condition.

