### Study Population and Study Flow

This study will recruit young adults aged 18 to 21 years living in or around New Haven, Connecticut. Recruitment efforts will focus on two distinct groups: (1) individuals who currently use nicotine-containing e-cigarettes, defined as use on 10 days or more within the past 30 days (*vapers*), and (2) individuals who report never having used nicotine-containing vapes (*nonvapers*). Participants who use nicotine in non–e-cigarette forms (eg, cigarettes and nicotine pouches) will not be excluded but will be assessed at baseline so that such exposure can be accounted for analytically. This design allows the comparison of psychophysiological cue reactivity between vapers and nonvapers, as well as the exploration of predictors of future initiation risk among nonvapers.

Eligibility will require participants to be fluent in English and able to provide informed consent. Exclusion criteria include self-reported photosensitive epilepsy, significant visual, hearing, or mobility impairment, current or recent (past 30 days) use of cannabis-containing e-cigarettes, current use of other illicit substances (eg, 3,4-methylenedioxymethamphetamine or ecstasy, and methamphetamine), nonmedical misuse of prescription drugs, or reliance on eyeglasses that are incompatible with VR eye-tracking hardware. These exclusions help reduce noise in psychophysiological responses that may arise from nonnicotine substances, ensuring clearer differentiation between the study groups. A total sample of 40 participants will be enrolled, which is sufficient for detecting medium group effects in VR cue-reactivity studies while accounting for potential data loss.

The study flow is shown in Figure 1. Eligible participants will complete a single laboratory session lasting approximately 1 hour. After providing informed consent and completing baseline questionnaires, participants will be fitted with a VR headset and biometric sensors. They will complete 3 VR scenes: a neutral baseline, a vaping cue scene without social pressure, and a vaping cue scene with social pressure in a counterbalanced order. Physiological data will be recorded continuously, and brief self-report measures (craving, presence, and social presence) will follow each cue scene. Participants will rate the system’s usability after finishing all the VR sessions. The session will conclude with a short semistructured interview, debriefing, and compensation.

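### If most never-vapers score 0 on the craving item, the craving group × cue condition interaction cannot separate greater sensitivity to social pressure in vapers from the floor of the scale, and the planned rank-based fallback makes this worse.

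*Protocol article*

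**What the plan says.** Table 2 of the Protocol article (Assessments) measures craving after each cue scene with a single item, "I have a desire for vaping/having an e-cigarette right now". The response is "A visual scale, ranging from 0", the anchor for no desire, up to 100.

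Under Study Population and Study Flow, the same item goes to vapers, "defined as use on 10 days or more within the past 30 days", and to nonvapers, "individuals who report never having used nicotine-containing vapes". The same section adds: "Participants who use nicotine in non–e-cigarette forms (eg, cigarettes and nicotine pouches) will not be excluded".

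Primary Aim lists craving among the psychological responses. It expects vapers to crave more than nonvapers in both scenes, and that "both groups will show stronger psychological and physiological responses in the social pressure condition than in the no pressure condition". It states no interaction hypothesis. Study Design nevertheless says "we powered the study for the group × cue condition interaction", without tying that to one outcome.

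Primary Analyses puts the outcomes through one 2×2 mixed ANOVA. If normality or equal variance fails, it moves to nonparametric alternatives such as the aligned rank transform (ART) ANOVA, so that the interaction can still be tested. Neither the assessment and analysis sections nor Limitations mentions a floor on the craving scale.

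**The concern.** Someone who has never vaped will often answer that they have no desire to vape right now. A group at the bottom of the scale has little or no room to register a difference between two scenes. If vapers' scores rise under pressure while never-vapers stay near 0, the 2×2 shows an interaction. That interaction then mostly restates the scene effect in vapers plus the lower limit of the scale.

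Two readings are at stake. A significant craving interaction could be taken to mean that vapers react more strongly to peers. A flat craving result in never-vapers could be taken to mean that pressure does not affect them. On this item, neither follows if most never-vapers score 0. The two planned analyses also differ in how they fail, and heavy zeros are what would trigger the switch from one to the other.

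**Working it through.** **1. The plan's own figure.** Inputs from Study Design: f = 0.25, r = 0.50, 2 groups, m = 2 measurements, power 0.80. Alpha is not stated; 0.05 is assumed. For the within-between interaction, λ = f²·N·m/(1−r), with 1 and N−2 degrees of freedom.

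- N = 34: λ = 0.0625 × 34 × 2 / 0.5 = 8.5, power 0.807.
- N = 32: λ = 8.0, power 0.781.
- N = 40: λ = 10, power 0.869.

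The stated minimum of 34 reproduces. With r = 0.50 the SD of a change score equals the SD of a single score, so f = 0.25 is a between-group difference in change of 1.0 SD.

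**2. Assumptions for craving.** None of these is in the protocol except the group size, r and the scale: 20 per group, r = 0.50, latent SD 25, vaper mean 40, the same latent pressure shift in both groups, scores clipped to 0-100. The true latent interaction is therefore zero. The share of never-vapers at 0 in the no-pressure scene is Φ(−μ/25), where μ is their latent mean: μ = 20 gives 21%, μ = 0 gives 50%, μ = −20 gives 79%, μ = −41 gives 95%.

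**3. What clipping does to an equal 15-point shift.** For never-vapers the expected score is μΦ(μ/σ) + σφ(μ/σ), with σ = 25.

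- 79% at 0: before, −20 × 0.2119 + 25 × 0.2897 = 3.0; after (μ = −5), −5 × 0.4207 + 25 × 0.3910 = 7.7. Observed change 4.7.
- 95% at 0: before (μ = −41), −41 × 0.0505 + 25 × 0.1040 = 0.5; after (μ = −26), −26 × 0.1492 + 25 × 0.2323 = 1.9. Observed change 1.4.
- Vapers, clipped at both ends: observed change 14.3.

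The apparent difference in change is 14.3 − 4.7 = 9.6 points (0.38 SD) or 14.3 − 1.4 = 12.9 points (0.52 SD), where the latent difference is zero.

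**4. How often the ANOVA interaction is significant (5% level).** A t test on change scores is equivalent to the 2×2 interaction test. 20,000 simulated studies per setting:

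| Never-vapers at 0 | Shift 5 | Shift 10 | Shift 15 | Shift 20 |
|---|---|---|---|---|
| 21% | about 5% | about 5% | about 5% | about 5% |
| 50% | 6% | 9% | 12% | 14% |
| 79% | 10% | 21% | 35% | 48% |
| 95% | 14% | 35% | 62% | 82% |

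Without clipping the rate is 5%. With no shift it stays near 5% at every floor level. A Welch test gives almost the same rates (20%, 34% and 47% for shifts of 10, 15 and 20 with 79% at 0), so a variance correction does not help.

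**5. The ART fallback.** With no scene effect at all, ART rejects the interaction in about 14%, 53% and 84% of studies at 50%, 80% and 95% zeros. A second set of runs with vaper mean 45 gave 15%, 62%, 86% and 93% at 50%, 84%, 94% and 99% zeros. The cause is ties: alignment gives all the zeros in a scene one common value, and a trivial difference between the two scenes' values becomes a uniform jump in rank. The fallback would probably be used here. In the 79% and 95% settings, a Shapiro-Wilk test on never-vaper scores rejected normality in every run, and Levene's test rejected equal variances in 98-100%.

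**The case against.** The strongest reply is that the floor share is not documented. The protocol nowhere says never-vapers will score 0, and it admits users of cigarettes and pouches, some of whom may report desire. At about 21% zeros there is no artefact, and at 50% it is modest. That stands, and it is why the point is conditional. A reader might infer that the interaction will appear whenever pressure acts equally on both groups. The figures do not support this: with 79% at 0 and a 10-point shift it is absent in 79% of studies.

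Second, shares of 79% and 95% at 0 imply latent means of about −20 and −41, below the anchor for no desire. If 0 means a true absence of desire, an interaction correctly describes observed craving. That also stands. Even then, it only restates that vapers' scores rise, and the both-groups hypothesis still has little to work with on this item.

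Third, a reader might infer that the protocol intends to claim greater sensitivity in vapers, or that its powered effect is undermined throughout. Neither is supported. Primary Aim has only group and scene hypotheses, and Study Design does not tie the powered interaction to craving. User-Centered Stimuli Design does limit how the scene contrast is read, but for context differences, not for the scale.

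Finally, the planned descriptives and Bonferroni-adjusted pairwise comparisons already supply part of the remedy. This is true. They do not supply the share at 0, the limit on interpretation, or a reason to avoid ART for craving.

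**Conclusion.** The point holds for craving and is conditional on a large share of zeros among never-vapers. With most of them at 0, the craving interaction does not identify differential sensitivity to social pressure, and the expectation of a stronger response in both groups is largely untestable on this item in never-vapers.

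Under ANOVA the size runs from negligible (about 5% at 21% zeros) to severe (up to 82% at 95% zeros). It requires a non-zero scene effect, which Primary Aim itself predicts, and a latent scale extending below no desire. Under ART the excess rejection needs no scene effect and comes from ties, a separate mechanism. The vaper mean, SD, shifts and floor shares are all assumptions.

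The sample-size calculation is arithmetically correct. The group difference in craving, the pilot's main question, is not threatened, and nothing here touches gaze, heart rate, electrodermal activity or presence.

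**What to change.** For craving only, make the prespecified estimates:

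1. the scene difference within vapers, paired, with a confidence interval;
2. the difference between groups in each scene, reported with the share of each group scoring 0.

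State that the craving interaction is not read as differential sensitivity to social pressure, that ART is not used for craving, and that the both-groups hypothesis is judged on gaze, heart rate, electrodermal activity and presence. Keep the 2×2 for those outcomes.

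The change affects analysis wording and what may be concluded, not data collection. With data from 7 of 40 participants collected by March 2026 (Results), it can still be fixed before most of the data exist. The cost is that the craving interaction is no longer a headline test.
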